**11.2 Secondary Efficacy:**

1) Rate of patients with negative SARS-CoV-2 on nasal or throat swab in a 2-day continuous real time RT-PCR test beginning from ‘first day of clinical recovery’ (see above) or ‘Day 10 after onset of symptoms depending on whichever of the two time points is first achieved

2) Timelines (days counted from onset of illness) - normal body temperature <37◦C, absence or minimal cough (see ‘clinical recovery’ for the definition), absence of dyspnoea (respiration rate 24/minute or less on room air), onset of clinical pneumonia, pneumonia diagnosed on chest X-Ray or CT scan, time to supplemental oxygen, admit in intensive care unit, mechanical ventilation (non-invasive), mechanical ventilation (invasive), steroid use, respiratory failure, adult respiratory distress syndrome, cytokine storm syndrome, secondary infection, shock, septicaemia shock, hospital discharge, death, negative nose or throat swab confirmatory test, all-cause mortality (Time Frame: up to 28 days).

Note: In case of symptoms, the absence on improvement should be sustained for at least 72 hours or live hospital discharge, whichever comes first.

3) Proportion OF patients developing an event that reflects clinical or otherwise improvement of worsening (the events are similar to those listed under Timelines, see above)

4) Improvement on pulmonary function tests using simple ‘home expiratory spirometer’ device and peripheral pulse oximetry

5) Improvement in selected laboratory parameters: blood haemoglobin, differential and total leukocyte counts, liver enzymes, renal functions, acute phase reactants, serum IL-6 and other selected cytokines, serum muscle enzymes (CK, CPK), serum ferritin, serum d-Dimer, anti-oxidant markers, serum BNP (cardiac function)

6) Serological Protective Antibody Assay (IgM and IgG)

7) Radiological Improvement on digital chest Xray and HRCT chest

8) Drug related: side effects and toxicity, and tolerability

9) Health status: WHO QOL (Appendix M) brief, health related behaviour habit and fitness questionnaire based on visual analogue scale (See Appendix N)

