**17.1 Sample Size:**

A convenience sample size of 70 patients in each of the arm is selected. The total sample size will be 140 patients in each of the 3 studies. The sample size is not based on any power calculations but by consensus within the experts of the Working Group constituted for the purpose of this protocol. It is assumed that the withdrawal rate may be in the range of 15-20%.

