**17.2 Statistical Analysis:**

Whenever suitable, both completer and an intent-to-treat analysis with ‘last observation carried forward’ will be performed; for intent-to-treat analysis the patient should have completed at least 4 weeks of intervention and completed the follow up visit at 4 weeks post enrollment.

All statistical processing will be performed using SPSS & BMDP software unless otherwise stated.

The data will be individually analyzed for central tendencies (mean, median), range, standard error, standard deviation and 95% confidence intervals for each intervention arm in each of the groups in the study. Data will be tabulated and graphically shown using standard format and MS Excel and other software programs. Though ANOVA will be used for most of the measures, standard parametric (Student t-test) and non-parametric statistical tests (Mann Whitney statistic, Kruskal Wallis test) will be used depending upon the normality of the data. Fisher’s exact test or Chi Square will be used to test the proportion of patients classified as efficacy failures and those with AE (calculate exact binomial 95% Confidence Interval).

The primary efficacy measures of ‘mean time to clinical recovery’ and ‘proportion of patients with clinical recovery’ in the two arms will be compared using appropriate statistical tests; ANOVA for ‘mean time’ and two proportion z-test for proportion of patients.

Secondary efficacy measures in the two arms will also be compared and Bonferroni correction will be applied for multiple comparisons.

Risk ascertainment will be done for selected variables. Regression analysis (multivariate and step down) will be used to identify predictors for important outcomes. Survival analysis will be carried out to compare the two interventions (HCQ and Ashwagandha) for primary efficacy at different study time points.

Within arm efficacy will be evaluated by a one sample Student t-test.

Significance for each statistical test result will be considered at two-sided p< 0.05.

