**19.8 Other Documentation**

All the investigators will supply the Principal Investigator with the following:

1. A current signed and dated CV for the investigator and his/her entire study team.
2. Documentation of Independent Ethics Committee’s approval. This should be accompanied by the EC working procedures and the EC Membership List. All these documents should be signed by the EC chairperson or designate.
3. Any local laboratory reference ranges used during the study
4. Copy of the EC approved consent forms (English and local versions)

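### Section 17.2 fixes no scale, baseline adjustment or arm-difference estimate for the skewed laboratory markers; a log-scale ANCOVA would be more powerful and would supply one

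*Combined protocol and SAP*

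**What the plan says.** Section 4 makes the effect on surrogate markers the first secondary objective. Section 11.2 item 5 turns this into an endpoint: "Improvement in selected laboratory parameters". It then lists, among others, acute phase reactants, IL-6 and other cytokines, ferritin and D-dimer. It does not say whether the follow-up level, the change from baseline or the ratio to baseline is compared.

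Section 17.2 sets the method: "Though ANOVA will be used for most of the measures", with Student t or rank tests (Mann-Whitney, Kruskal-Wallis) depending on normality. No normality test or threshold is named. The summaries include "95% confidence intervals for each intervention arm". No interval for the difference between arms is specified for these markers. The regression planned there is for finding predictors of outcome, not for comparing arms on a marker. Secondary measures carry a Bonferroni correction, with the number of comparisons not given.

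On size, Section 17.1 says "A convenience sample size of 70 patients in each of the arm is selected" and "The sample size is not based on any power calculations". On laboratories, the only indication is a filing item in Section 19.8: "Any local laboratory reference ranges used during the study".

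**The concern.** Markers such as CRP, ferritin, D-dimer and IL-6 are positive and can be expected to be right-skewed. On the raw scale a few very high values dominate both the mean and its standard error. If improvement is read as raw change, patients with high baselines dominate as well. The one-sample t-test that Section 17.2 plans within each arm makes raw change a natural reading.

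Two things are at stake. The first is power that the same data would yield under a better-chosen model. The second is the result itself. In an exploratory trial with no power calculation, the size and precision of the arm difference is the main product for a secondary objective. Per-arm intervals and a rank-test p-value do not supply it. This second point needs no assumption about distributions.

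**Working it through.** **The plan's own figures.** 70 × 2 = 140 per trial, which is consistent. Section 17.1 also says "It is assumed that the withdrawal rate may be in the range of 15-20" per cent, leaving 70 × 0.85 = 59.5 to 70 × 0.80 = 56 per arm. Section 17.2 says "Significance for each statistical test result will be considered at two-sided p< 0.05". The plan states no marker SD, effect or power, so there is no power figure to reproduce.

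**Assumptions, none from the documents.** The marker is log-normal with log-SD σ = 0.8. The level on drug is 30% lower, so |ln 0.7| = 0.357. The baseline to follow-up correlation ρ is 0.3 or 0.6.

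**Formula check on the log scale.** Power = Φ(0.357 / (s√(2/n)) − 1.96), where s depends on the analysis:

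| Analysis | s | n = 70 | n = 56 |
|---|---|---|---|
| t-test on log follow-up | σ = 0.80 | 75% | 66% |
| Mann-Whitney on follow-up (n × 0.955) | 0.80 | 73% | 64% |
| Log ratio to baseline, ρ = 0.3 | σ√(2(1−ρ)) = 0.947 | 61% | 51% |
| Log ratio to baseline, ρ = 0.6 | 0.716 | 84% | 75% |
| Log ANCOVA, ρ = 0.3 | σ√(1−ρ²) = 0.763 | 79% | 70% |
| Log ANCOVA, ρ = 0.6 | 0.640 | 91% | 84% |

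**Raw follow-up ANOVA, n = 70.** With the SOC follow-up median set to 1:
- Difference in means: 0.3 × e^0.32 = 0.413.
- Variance on SOC: (e^0.64 − 1)e^0.64 = 1.70; on drug, 0.49 times that.
- SE = √(1.70 × 1.49 / 70) = 0.190.
- Power = Φ(0.413/0.190 − 1.96) ≈ 58%.

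**Raw change, n = 70, ρ = 0.6.** The difference to detect is still 0.413, but baseline variance enters in full.
- No overall fall: covariance (e^0.384 − 1)e^0.64 = 0.888. Variances are 1.70 + 1.70 − 2 × 0.888 = 1.62 (SOC) and 0.83 + 1.70 − 2 × 0.7 × 0.888 = 1.29 (drug). SE = √(2.91/70) = 0.204, and power is about 53%.
- Threefold fall: baseline variance becomes 9 × 1.70 = 15.3 and the covariance triples to 2.66. Variances are 11.7 and 12.4. SE = √(24.1/70) = 0.587, and power is about 10%.

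**Simulation.** Same assumptions, 70 per arm, with assay offset none or 2-fold at half the sites, and fall from baseline none or threefold. Results are at two-sided 0.05 before Bonferroni; repeat runs move by one or two points.

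| Analysis | Power across settings |
|---|---|
| ANOVA, raw follow-up | 52-63% |
| Mann-Whitney, follow-up | 63-72% |
| ANOVA, raw change | 9-56% |
| Mann-Whitney, raw change | 16-71% |
| t-test, log ratio | 59-85% |
| Log ANCOVA on baseline and site | 76-90% |

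Log ANCOVA gave 76-77% at ρ = 0.3 and 89-90% at ρ = 0.6.

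**Other inputs.** A separate set used 56 per arm, a true ratio of 0.6, log-SD 0.8 to 1.2, a threefold fall, and laboratory offsets of SD 0 or 0.3 on the log scale over seven sites. It gave 36-82% for raw follow-up ANOVA, 56-91% for Mann-Whitney on follow-up, 6-14% and 14-26% for raw change (ANOVA, Mann-Whitney), 48-97% for the log ratio, and 63-99% for log ANCOVA (61-98% with site terms). With Bonferroni over an assumed 20 tests (log-SD 1.0, ρ = 0.5, offset SD 0.3), power was 11% for raw follow-up ANOVA, 28% for Mann-Whitney, 36% for the log ratio and 49% for log ANCOVA (46% with site terms).

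**The case against.** The strongest reply is that the plan already deals with skewness. Its normality switch would send strongly skewed markers to a rank test, and ranks are unchanged by taking logs. This largely stands. On the same follow-up values Mann-Whitney loses only 1-4 points to a log-scale t-test. In the 56 and 70 per arm runs with true ratio 0.6, an assumed Shapiro-Wilk switch at 0.05 gave the same power as Mann-Whitney throughout. A reader might infer that both planned tests discard much of the power because of the scale alone. That is right for ANOVA and for raw change, but not for a rank test on follow-up values. That test's shortfall against log ANCOVA comes mainly from ignoring baseline.

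A reader might also infer that the remedy is the log of follow-up over own baseline. It is not uniformly better. Its variance, 2σ²(1−ρ), is below σ² only when ρ exceeds 0.5. At ρ = 0.3 it has 59% power against 72% for Mann-Whitney. The documents give no correlation, and visits run to week 12, well after expected recovery, so a high value cannot be presumed.

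Finally, a reader might take it as stated that raw values from different local laboratories are pooled. Section 19.8 asks only for any local ranges used and does not say where these markers are assayed. The central facility in Section 17.3 is for data entry, and the available text names no central laboratory. Local laboratories and raw units are reasonable inferences, not stated rules.

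It is also true that this is one of nine secondary items in a deliberately unpowered trial, and that Bonferroni lowers every power figure. Neither point supplies the missing endpoint definition or the missing arm-difference estimate.

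**Conclusion.** The concern holds in a limited form. From the text alone, the marker endpoint is undefined, the test depends on the observed data under an unstated rule, and no between-arm estimate, log scale, baseline adjustment or site term is specified.

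The size of the power loss is conditional on right-skewed markers and on the assumed SD, correlation, effect and fall from baseline. Under the main assumptions, log ANCOVA with site beat every planned option in each setting: 76-90%, against 52-63% for raw follow-up ANOVA and 63-72% for Mann-Whitney on follow-up. Raw change ranges from slightly below these to very poor (ANOVA 9-56%, Mann-Whitney 16-71%), depending on how far levels fall in both arms. The figures illustrate the choice of method and do not predict this trial's power.

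**What to change.** In Section 17.2, name the laboratory markers to be treated as skewed and the visit compared. Prespecify one model for them: ANCOVA of log follow-up on log baseline, with treatment arm and site as terms. Report the drug/SOC ratio of geometric means with its 95% CI, in place of a test chosen after looking at normality. In Section 11.2 item 5, define improvement to match. Do not substitute the unadjusted log ratio.

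As an illustration of what this yields, with log-SD 0.8, ρ = 0.6 and 70 per arm, SE = 0.64 × √(2/70) = 0.108. An observed ratio of 0.70 would then carry a 95% CI of exp(−0.357 ± 1.96 × 0.108), about 0.57 to 0.87.

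The site term and baseline adjustment also guard against laboratory differences if they exist. The cost is SAP wording with no new data, plus one fixed substitution rule for values below the assay limit.

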# 5. STUDY DESIGN

Fig 1 shows the study flow and the overview of study design and timelines, and principal study events including clinical examinations, laboratory and other investigations.

Each of the three selected and standardized Ayurveda drugs i.e. **AYUSH 64 (A-64), Sanshamani Vati Plus (SV +)** and **Yashtimadhu (MYT)** will be assessed as add on or adjunct treatment in three different drug trials of two arms each for efficacy and safety under a common current protocol.

Each of the drug trial will be a randomized, prospective, open label, parallel efficacy, active control two arm multicentre study. Each of the three Ayurveda drugs is being considered as an adjuvant drug to Standard of Care (SOC). The SOC and Ayurveda drug combination is the experimental interventional arm which will be compared to the active control arm of standalone SOC. The total duration of each of the three drugs’ study is 12 weeks and this period includes time to clinical recovery (defined later in text) and a period of follow up to complete 12 week of observation following admission to the hospital. The nature of SOC and any follow up medication will be decided by the treating physician. Some variation in SOC between different study sites and even between patients is possible. The study investigators will meticulously record the details of SOC in the study case record form of each patient. The dose of Ayurvedic drugs is as per standard Ayurveda practise and decided by consensus amongst experts in the AYUSH working group for this patient. The total sample size of each drug study is 140 patients with 70 patients randomized to each arm.

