# CONSENT, SELECTION, SCREENING, and ENROLLMENT

Study patients will be served on first come first serve basis as per the protocol.

Consenting and eligible patients will be enrolled as soon as possible in a COCID-19 management facility and the study intervention begun. It is important that symptomatic patients suspected for COVID-19 on clinical grounds are quickly evaluated for eligibility. It is important to enroll the patient as close to the onset of symptoms as possible. As described above, this study is dealing with patients of COVID who are ‘non-emergent’ which means mild and moderate disease (pneumonia) which does not require emergency or critical care (see section on inclusion and exclusion criteria).

An ‘Patient Information Sheet’ (Appendix F) in the language understood by the patient will be provided to each patient for study and discussion prior to enrollment. The information fact sheet will describe the overall design of the study and the rationale, benefit and side effect profile of the study drug interventions, and other aspects of the study.

Patients will be selected from the outpatient or inpatient facility in COVID-19 medical centres/ hospitals. The study will be explained to the volunteer patients and those willing to sign the informed consent (Appendix G) will be screened for eligibility as per the inclusion and exclusion criteria in the protocol.

Though it will be preferable to enrol patients with diagnosis confirmed by a positive RT-PCR assay using a nasal or throat swab in a standardized procedure, a patient with a clinical diagnosis of COVID- 19 as described below will be eligible.

Eligible patients will be enrolled using a simple randomization table (provided to the investigator) in a block of 20 patients each to either of the two study arms - SOC plus Ayurveda drug or SOC. As the target sample size is 70 patients in each arm, the first block of randomized allocation will be of 10. The study randomization will be carried out by the investigator.

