**DATE OF INFORMED CONSENT__________LANGUAGE OF INFORMED CONSENT ________**

**STUDY GROUP:** □ **STANDARD OF CARE** □**AYURVEDA**

Name of Drugs_____________________________________________________

ADMISSION DATE TO HOSPITAL___________________________________

STATUS OF DISEASE ON ADMISSION: □ MILD □MODERATE

Note: Please check ‘INCUSION and EXCLUSION CRITERIA’ on page 4

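### Days to recovery is compared without adjustment for illness duration, severity or site, all of which are recorded; this probably costs precision, by an amount the documents cannot fix

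*Combined protocol and SAP*

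**What the plan says.** Section 17.2 compares the two primary outcomes between arms by "ANOVA for ‘mean time’ and two proportion z-test for proportion of patients". An ANOVA could hold further factors, but none is named. Regression is planned only to find predictors of outcome, by a step-down procedure. A survival analysis of primary efficacy is mentioned without covariates, and it names two drugs that are not in this trial. The testing rule is "Significance for each statistical test result will be considered at two-sided p< 0.05".

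Section 17.1 fixes the size: "A convenience sample size of 70 patients in each of the arm is selected", and "The sample size is not based on any power calculations but by consensus within the experts of the Working Group". On losses it adds "It is assumed that the withdrawal rate may be in the range of 15-20" per cent.

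Section 11.1 counts days from randomisation to clinical recovery, over a frame of up to 28 days. The secondary timelines in Section 11.2 count from onset of illness.

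The case record form (Appendix H) has fields for date of onset and study site, and the item "STATUS OF DISEASE ON ADMISSION: □ MILD □MODERATE". On care, Section 5 says "Some variation in SOC between different study sites and even between patients is possible". On allocation, the section on consent, selection, screening and enrolment says "Eligible patients will be enrolled using a simple randomization table (provided to the investigator) in a block of 20 patients each". It names no stratification by duration, severity or site.

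**The concern.** Patients enter at different points of an illness that mostly resolves by itself. Because the primary clock starts at randomisation, someone enrolled late in the illness may have fewer days left than someone enrolled early, whatever the treatment. The enrolment section asks for entry close to onset, but Section 10 sets no maximum. Severity and local care may also shift recovery time.

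If these variables predict days to recovery, an analysis by arm alone leaves their contribution in the error term and widens the interval on the treatment effect. The sample was chosen by consensus and cannot easily grow, so adjustment is one of the few ways to gain precision without more patients. Naming the covariates beforehand also matters. If the arms happen to differ in days since onset, an adjustment chosen after the data are seen, or by a step-down search, will be less credible.

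**Working it through.** **No figure to reproduce.** The plan states no power, effect size or SD. Only 2 × 70 = 140 can be checked, and it agrees.

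**Inputs**
- n = 70 per arm; with 20% withdrawal, 0.80 × 70 = 56 (Section 17.1).
- Two-sided alpha 0.05 (Section 17.2).
- SD of days to recovery: *assumed*. The one recovery row in literature Table 2 gives a median of 10 days (IQR 7 to 14), so SD ≈ (14 − 7)/1.349 = 5.19 days. The table does not say when that clock starts. Range considered: 4 to 7 days.
- Difference of 2 days: *assumed*.
- Correlation rho between days since onset (or the covariates together) and days to recovery: not in the documents, so shown as a range.

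**Power.** SE = SD × √(1 − rho²) × √(2/n); power ≈ Φ(2/SE − 1.96).

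Unadjusted at n = 70: SE = 5.19 × √(2/70) = 0.877; 2/0.877 − 1.96 = 0.32; power 63%.

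| rho | R² | SE ratio | Power, 70 per arm | Power, 56 per arm |
|---|---|---|---|---|
| 0 (unadjusted) | 0 | 1.000 | 63% | 53% |
| 0.2 | 0.04 | 0.980 | 64% | 55% |
| 0.3 | 0.09 | 0.954 | 67% | 57% |
| 0.5 | 0.25 | 0.866 | 75% | 65% |

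The choice of SD matters. At 70 per arm, going from no adjustment to rho 0.5 takes power from 84% to 93% with SD 4, and from 39% to 50% with SD 7.

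**Where rho might lie.** Table 2 gives onset to admission as median 7 days (IQR 4 to 8), so SD ≈ 4/1.349 = 2.97. If total illness length were independent of enrolment day, rho would be 2.97/5.19 = 0.57 in size. That independence cannot hold exactly, because only patients still ill can enrol. A simulation used assumed gamma distributions, with enrolment day of mean 6.5 and SD 3, and kept only patients still ill at enrolment. It gave rho of about 0.2 if the recovery row counts from onset (mean about 10, SD 5.2) and about 0.5 if it counts from admission. With a roughly constant recovery hazard, rho is near 0.

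**Cost of adjusting.** The table does not charge for estimating covariate terms. Break-even R² is roughly k/(N − 2) for k terms: 5/138 ≈ 0.04 and 8/138 ≈ 0.06. So at rho 0.2 (R² 0.04) a five-term model only about breaks even, whereas one continuous term costs 1/138 ≈ 0.007. In simulation at N = 140, useless covariates cost about 1 to 2 points of power, and type I error with adjustment stayed between 4.3% and 5.4%.

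**Recovery proportion.** Comparing the raw risk difference with a logistic-standardised one in simulation (N = 140), the ratio of adjusted to unadjusted SE was 0.92 to 0.97 at a control rate of 60% or 80%, and 0.99 to 1.01 at 95%.

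**The case against.** Unadjusted tests are valid here. The trial is declared exploratory and unpowered, no stratification factor is being ignored, and nothing in the plan contradicts itself on this point. All of that stands, and it makes this an efficiency point rather than an error.

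The objections to size also largely stand. A reader might infer a 33% cut in variance (0.57²) and power near 79%. That rests on the independence assumption that fails when only ill patients enrol, and on a recovery row with no stated clock. The 2.97-day spread comes from a hospital cohort, and the request to enrol early may narrow it: with SD 1.5 to 2 days the same ratio gives rho 0.29 to 0.39, an R² of 8 to 15%. The exclusion list in Appendix H (though not Section 10) also has an item on daily fever for more than 72 hours, which would narrow the spread further if applied; the two lists need reconciling.

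A reader might assume that severity and site add to the gain. Section 2 contrasts mild with severe disease, and severe patients are excluded; no mild-versus-moderate difference is given. Section 5 calls variation in care possible, and the text available gives no site count. Nor does the plan say that each site has its own randomisation table, so balance within site cannot be presumed.

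Being exploratory does not remove the point. The plan still tests at p < 0.05, and the synopsis calls the sample sufficient for meaningful conclusions.

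**Conclusion.** The point holds for days to recovery, as a probable loss of precision of uncertain size. Under the assumed SD of 5.2 days and a 2-day difference at 70 per arm, adjustment takes power from 63% to between about 64% (rho 0.2) and 75% (rho 0.5), before the small charge for extra terms. If the covariates explain nothing, it loses about 1 to 2 points.

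Two stronger readings are not supported. First, a reader might take chance imbalance in days since onset as bias. Under random allocation the unadjusted standard error already allows for it. This presumes that allocation is random: the opening of Section 17 calls the design non-randomised, against the title and Section 5, and that must be reconciled. Second, a reader might think both primary comparisons suffer alike. Section 8 expects the large majority to recover completely, and most to be discharged within 5 to 15 days, so the recovery proportion may sit near its ceiling, where adjustment gains about nothing.

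**What to change.** In Section 17.2, pre-specify for days to recovery:
- days from symptom onset to randomisation, continuous and derived from the two dates, as a covariate;
- mild/moderate status on admission as a covariate;
- site as a factor with small sites pooled, or as a stratum.

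Use these in whichever recovery-time model is adopted. That choice must also settle how patients not recovered by day 28 or withdrawn are handled, because a linear regression on days does not define their value. Keep the unadjusted test as supportive.

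For the recovery proportion, a covariate-standardised risk difference is optional. Near 95% recovery, sparse site cells could cause separation, so omit site there or keep the unadjusted z-test.

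The cost is a few degrees of freedom, a change of wording and a little more analysis. No new data are needed.

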**d. The investigational products:**

Three formulations will be used in the study; those will be separately used as adjunct treatment. These formulations are –Samshamani Vati Plus, AYUSH 64 and Yashtimadhu.

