**2.6 Management (Table 6)**

There is no specific drug management of proven value in the treatment of COVID-19. The emphasis is on symptomatic and timely supportive management.

Patients with mild disease do not require hospital-based interventions and can be managed with at home with some isolation to contain the virus transmission. Patients with severe disease and complication like severe acute respiratory infection (SARI), acute respiratory distress syndrome (ARDS), sepsis and septic shock are best managed in an intensive care unit (ICU) and may require oxygen supplement, mechanical ventilation, intravenous antibiotics and other critical hemodynamic and respiratory support. Use of corticosteroids is reserved for progressive severe disease and is not routinely recommended. However, of late, steroids have been observed to contribute to relief of symptoms and promote early recovery when initiated early in moderately severe disease but evidence is still lacking in this regard (19).

The Ministry of Health and Family Welfare GOI has issued guidelines on the clinical management of COVID-19 on 31^st^ March 2020 (20). These guidelines also mention an empirical short use of Hydroxychloroquine (HCQ) in conjunction with azithromycin in the management of COVID 19. The latter is not supported by management guidelines issued by WHO (19). US FDA recently issued a warning against routine use of HCQ in COVID-19.

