# 11. EFFECTIVENSS MEASURES

**11.1 Primary Efficacy:**

1. Mean time (days) for clinical recovery (Day of randomization to the Day of clinical recovery (see criteria below] [Time Frame: up to 28 days]
2. Proportion of patients showing ‘clinical recovery’

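### Time to clinical recovery is compared by ANOVA with no value set for patients who do not recover by Day 28, are withdrawn or die, and the only survival analysis names the wrong arms

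*Combined protocol and SAP*

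**What the plan says.** Section 11.1 lists the first primary outcome as "Mean time (days) for clinical recovery", counted from randomisation, with "Time Frame: up to 28 days". The second is the proportion of patients who recover.

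Section 17.2 assigns the tests: "ANOVA for ‘mean time’ and two proportion z-test for proportion of patients". Earlier in that section, rank tests are the fallback for non-normal data: "Mann Whitney statistic, Kruskal Wallis test) will be used depending upon the normality of the data". The same section later adds: "Survival analysis will be carried out to compare the two interventions (HCQ and Ashwagandha) for primary efficacy at different study time points". It names no survival method, no censoring rule and no order of precedence over ANOVA.

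Four other provisions bear on this:
- Section 17.1: "It is assumed that the withdrawal rate may be in the range of 15-20" per cent.
- Sections 9, 10 and 14 withdraw patients who progress to severe disease. Section 9 asks investigators to stay in contact with them to 12 weeks and to record, among other things, time to recovery and death.
- Section 17.2 admits a patient to the intention-to-treat analysis only after four weeks of intervention and the four-week visit, with last observation carried forward.
- The synopsis names the products as "Samshamani Vati Plus, AYUSH 64 and Yashtimadhu". Each is added to standard of care (SOC) and compared with SOC alone.

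**The concern.** A patient who has not recovered by Day 28 has no recovery day. Nor has one who dies first, or one who leaves and is not followed. ANOVA, the t-test and the rank tests all need a number for every patient analysed, and the plan does not say which number these patients get. The analyst must choose after the data are in: drop them, enter the last day seen, or enter Day 28. These choices estimate different things.

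The gap matters because the missing values are not a random subset. Patients who worsen are withdrawn, and the four-week rule removes early deaths and early withdrawals from the set called intention-to-treat. The treatment is open label, so withdrawal could also differ between arms. Section 17.2 has one sentence that could supply a censoring-aware analysis, but it names a comparison that none of the three trials makes. This affects the first primary outcome of all three trials.

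**Working it through.** The plan gives no figure to reproduce for this outcome: 70 per arm is stated as a convenience sample, with no effect size or SD.

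**1. How many recovery times may be missing**
- Withdrawal (Section 17.1): 140 × 0.15 = 21 and 140 × 0.20 = 28 patients.
- Unrecovered at Day 28: Table 2 has one recovery figure, median 10 days (IQR 7-14). A lognormal fit has σ = ln(14/7)/(2 × 0.6745) = 0.514, so P(T > 28) = 1 − Φ(ln 2.8/0.514) = 2.3%. An exponential with the same median gives 0.5^(28/10) = 14.4%. The choice of shape is an assumption.

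**2. Recovered patients only, against all patients to Day 28**

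Assumed per 100 patients: 80 in each arm recover at 10 days. Under SOC the other 20 do not recover by Day 28. Under the drug, 15 of those 20 recover at about Day 24.

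| Quantity | SOC | SOC + drug |
|---|---|---|
| Mean among recovered | 10.0 | (80×10 + 15×24)/95 = 12.2 |
| Restricted mean to Day 28 | (80×10 + 20×28)/100 = 13.6 | (80×10 + 15×24 + 5×28)/100 = 13.0 |
| Proportion recovered | 80% | 95% |

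The mean among recovered patients is 2.2 days worse for the arm in which more patients recover. The restricted mean is 0.6 day better.

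If only 5 of 100 SOC patients are unrecovered and the same three-quarters are rescued:
- Recovered only: 10.0 v (95×10 + 3.75×24)/98.75 = 10.5.
- Restricted means: (95×10 + 5×28)/100 = 10.90 v (95×10 + 3.75×24 + 1.25×28)/100 = 10.75.

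The reversal remains but shrinks to about 0.5 day.

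**3. Withdrawal with no true drug effect**

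Simulation with 70 per arm and 2,000 runs per scenario. Assumed: lognormal recovery times as in step 1, a Day 28 cut-off, and withdrawal spread evenly over the first 14 days. Entries are the share of trials with two-sided p < 0.05.

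| Withdrawal | ANOVA, recovered only | ANOVA, withdrawal day used as recovery day | Log-rank |
|---|---|---|---|
| 17.5% in both arms, unrelated to recovery | 4.0% | 4.0% | 4.4% |
| 10% v 25%, unrelated to recovery | 5.6% | 12.6% | 4.4% |
| 10% v 25%, slow recoverers only | 17.2% | 31.2% | 8.2% |

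In the last row the two ANOVA versions show false differences of about −0.9 and −1.3 days, favouring the arm that loses more slow patients. The log-rank test also exceeds 5% there, so changing the test is not enough. Recovery data after withdrawal have to be used.

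**4. The survival sentence**

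The randomised comparison is SOC plus one of three named formulations against SOC. HCQ and Ashwagandha are not randomised in any of the trials. The adverse event form in Appendix Q carries the same pair, which suggests text carried over from another protocol.

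**The case against.** - **The plan does not restrict ANOVA to recovered patients.** This is correct. A reader might infer that it does, but Section 17.2 never says so. If non-recoverers were entered at Day 28, ANOVA would estimate the same difference as the restricted mean. The defect is a missing rule, which leaves a biased choice open.
- **The second primary outcome would expose a reversal.** It would in the step 2 example: at 70 per arm, a z-test of 80% v 95% favours the drug in roughly 75-81% of simulated trials. The two primary results would then conflict, and the plan has no rule for that. A reader might still infer that the trial's overall answer would have the wrong sign; the documents do not support that.
- **The example is adverse.** It is. Twenty per cent unrecovered is high for mild to moderate disease, since Section 8 expects most patients home within 5-15 days. How often the recovered-only comparison would be significantly against the better arm depends on an SD that the plan does not give: about 88% of trials at SD 2 days, 60% at SD 4 and 43% at SD 6. At SD 4 it falls to about 10% with 5% unrecovered, and 4% with 2%. No single rate should be quoted.
- **Survival analysis was intended, and HCQ may be in use.** Both are fair. The sentence is aimed at primary efficacy. On the national guidance generally followed as SOC, Section 2.6 says: "These guidelines also mention an empirical short use of Hydroxychloroquine (HCQ) in conjunction with azithromycin". So HCQ may be background care, though not a randomised arm. As written, the sentence still cannot be carried out.
- **The trial is exploratory.** That lowers the stakes, but the plan still presets two-sided p < 0.05 and expects meaningful conclusions.

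**Conclusion.** The point stands as a fault in the analysis text that needs correcting before any data are analysed. A primary time-to-recovery outcome cut off at Day 28 has no rule for patients without a recovery day, and its only survival analysis names the wrong comparison.

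The size of the bias is conditional. It can reach about 2 days in the wrong direction if non-recovery is common, the drug produces late recoveries and only recovered patients are averaged. It can produce false positives in 17-31% of trials if slow recoverers are withdrawn unequally (10% v 25%). It is small if non-recovery is rare, or if withdrawal is equal and unrelated to recovery. The recovery distributions, withdrawal timing and arm-specific rates behind these figures are assumptions, not protocol values.

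A reader might also infer from Appendix J, which stops at D20 and has a fever row but no temperature value, that recoveries on Days 21-28 would leave no daily record. That goes too far. Section 7 uses the hospital case sheet, Appendix A calls for daily vital parameters, and the Section 19.3 app records symptoms daily throughout the study. The study's own sheet falls short of the outcome window, which is a minor gap.

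**What to change.** In Section 17.2:
1. Replace ANOVA with one named primary analysis comparing SOC plus the trial's Ayurvedic drug with SOC, from randomisation to Day 28. A suitable choice is the difference in 28-day restricted mean time to recovery with a 95% CI, supported by a log-rank test. This keeps the outcome in mean days.
2. Include every randomised patient, and drop the four-week completion condition for this analysis.
3. Count a patient who dies before recovery as not recovered through Day 28, rather than censoring at death.
4. For patients withdrawn on progression, use the recovery and death information that Section 9 already asks for. Censor only those truly lost to follow-up. Fixing progression as non-recovery would discard real recoveries.
5. Delete the reference to HCQ and Ashwagandha.
6. Optionally, add a Cox model adjusted for baseline variables already on the case record form, as a supporting analysis.

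As a minor form change, extend Appendix J to D28 and add a temperature value and the date on which the recovery criteria were first met.

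The cost is analysis wording and one revised form page, with no extra patients or procedures. The analysis does rely on Section 9 follow-up being complete enough to date recovery after withdrawal. Section 10 only encourages that follow-up, so the two sections should be aligned.
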